## Abstract

**Introduction:**

Children with congenital hemiplegia often present with limitations in using their impaired upper limb which impacts on independence in activities of daily living, societal participation and quality of life. Traditional therapy has adopted a bimanual training approach (BIM) and more recently, modified constraint induced movement therapy (mCIMT) has emerged as a promising unimanual approach. Evidence of enhanced neuroplasticity following mCIMT suggests that the sequential application of mCIMT followed by bimanual training may optimise outcomes (Hybrid CIMT). It remains unclear whether more intensely delivered group based interventions (hCIMT) are superior to distributed models of individualised therapy. This study aims to determine the optimal density of upper limb training for children with congenital hemiplegia.

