**Methods and analyses:**

A total of 50 children (25 in each group) with congenital hemiplegia will be recruited to participate in this randomized comparison trial. Children will be matched in pairs at baseline and randomly allocated to receive an intensive block group hybrid model of combined mCIMT followed by intensive bimanual training delivered in a day camp model (COMBiT; total dose 45 hours direct, 10 hours of indirect therapy), or a distributed model of standard occupational therapy and physiotherapy care (SC) over 12 weeks (total 45 hours direct and indirect therapy). Outcomes will be assessed at 13 weeks after commencement, and retention of effects tested at 26 weeks. The primary outcomes will be bimanual coordination and unimanual upper-limb capacity. Secondary outcomes will be participation and quality of life. Advanced brain imaging will assess neurovascular changes in response to treatment. Analysis will follow standard principles for RCTs, using two-group comparisons on all participants on an intention-to-treat basis. Comparisons will be between treatment groups using generalized linear models.

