There is currently little evidence to support traditional standard care block models of upper limb therapy (e.g. six to eight weekly one hour sessions), as these alone are unlikely to provide an adequate dose to drive changes in upper limb function. Occupational therapy home programs have been shown to be effective in a high quality randomised controlled trial [26] and could allow an adequate dose of therapy to be achieved if accompanied with a distributed block model of intervention. As little as 15 minutes of home program practice four times per week over an eight week block of therapy was shown to be effective in improving functional goals and quality of upper limb skills (Quality of Upper Extremity Skills Test) [26]. It remains unclear whether a more intensive model of upper limb training is superior to a distributed standard care model augmented by a functionally focused home program to achieve a similar dosage of therapy to improve upper limb unimanual, bimanual and individualized outcomes.

This current study proposes a hybrid model which will sequentially combine modified constraint induced movement therapy (mCIMT) followed by intensive bimanual training (called COMBiT) and compare this to a standard upper limb training model in a randomised trial. We propose to compare the intensive group based COMBIT model (one week of 30 hours of mCIMT followed by one week of 30 hours of bimanual training of which 45 hours was direct and 10 hours of indirect upper limb training) to standard care delivered in an individualised and distributed model (standard occupational therapy (OT); total dose 45 hours direct and indirect over 12 weeks) for improving outcomes as they pertain to activity and participation for children with congenital hemiplegia. Standard care for children with congenital hemiplegia will be six weekly sessions of 1.5 hours of OT provided in an individualised format (9 hours direct) in combination with an individually designed home program delivered over a 12 week period (36 hours indirect training). Each approach, COMBiT or standard care may follow intramuscular BoNT-A injections to the forearm provided as part of standard clinical practice that is delivered to reduce forearm spasticity prior to upper limb training.

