### Study interventions

For the COMBiT day camp group, we plan to provide treatment in groups of 10–15 children over ten days. The initial five consecutive days will focus on mCIMT. After a weekend, BIM will be provided for the next five consecutive days. Therapy will comprise 45 hours direct upper limb training and 10 hours of indirect training in more general gross motor upper limb activities. COMBiT will have a novel circus theme. This intensive COMBiT therapy will be compared to standard care which involves individually tailored therapy in a distributed model for 1.5 hours per week for six weeks. This involves six hours individual therapy with OT/PT and three hours of home program demonstration (nine hours direct UL therapy). The home programs (completed by participants in their home/community environment) will comprise 30 minutes daily home practice six days/week for 12 weeks (36 hours indirect UL therapy). The COMBiT and the standard care programs will have the same dosages of upper limb therapy (COMBIT: 45 hours direct UL training; Standard care (SC): nine hours direct UL training and 36 hours indirect UL therapy). They will differ by (i) delivery method (block, group model versus distributed individualised model) (ii) varied construct (mCIMT versus goal directed training) and (iii) different environment.

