COMBiT will be conducted over two weeks of the school holidays in a “day camp model”. Participants will attend a community facility “Flipside Circus” for six hours a day, five days a week from 9am to 3pm. In total, 45 hours of the day camp program will directly target upper limb training, and 10 hours will provide indirect use of the UL in more general gross motor upper limb activities. For both mCIMT and BIM training, the content will include intensive activity based practice, circus activities as well as self-care and recreational activities. The group will be led and supervised closely by five to seven therapy staff to achieve a ratio of one trainer to two children. Five core occupational therapists and one physiotherapist will plan and lead all intervention groups. Daily grading of activities and modification of tasks for the participants in each group will be performed by the core therapists. Tasks and activities will focus on reducing upper limb activity limitations identified at baseline assessment and target three occupational performance goals identified by the parents and/or child. Planning activities for each group will require task analysis, and develop guidelines for grading to challenge children with varying capabilities. Specific details of the content of the COMBiT weekly program contents are presented in Additional file 1: Table S1. Prior to commencement of the daily program, staff will be briefed and given specific tasks with written instructions outlining how each activity will be performed for the specific children they are supervising. Professional circus trainers will lead the two hour circus workshops. The core therapy team will meet with the circus trainers to design these programs and at the end of each session to discuss and modify the program as required and provide guidance to grading of tasks for participants. A debriefing session for the entire COMBiT group with staff members and separately for the staff and volunteers will be conducted at the conclusion of each day. The core therapy team will also meet daily to review individual participants’ goals and continually grade their program. A daily record of attendance will be kept and anecdotal information from the day will also be recorded.

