## Discussion

This paper presents the background and design for a matched pairs randomized trial comparing an intensive block of combined mCIMT and BIM training (COMBIT) to a distributed standard care model of upper limb rehabilitation for children with congenital hemiplegia. To our knowledge this is the first study to directly compare the density of upper limb training, a block of intense COMBiT compared to an equal dose of a distributed model of individualised training. Furthermore, we will be evaluating the outcomes of the intervention program across all domains of the ICF using valid and reliable measurement tools.

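### The arms are called equal in dose, but by the protocol's own categories the planned hours are 55 against 45 in total and 45 against 9 direct, so a difference could not be credited to density at equal dose

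*Protocol article*

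**What the plan says.** Under Study interventions the protocol article states that "The COMBiT and the standard care programs will have the same dosages of upper limb therapy". The bracket that follows shows the count: 45 direct hours for COMBiT, and 9 direct plus 36 indirect hours for standard care. Earlier in the same section COMBiT is described differently: "Therapy will comprise 45 hours direct upper limb training and 10 hours of indirect training in more general gross motor upper limb activities". The Abstract (Methods and analyses) gives COMBiT as "total dose 45 hours direct, 10 hours of indirect therapy", against a standard care total of 45 hours, direct and indirect together.

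The Background describes COMBiT as "one week of 30 hours of mCIMT followed by one week of 30 hours of bimanual training of which 45 hours was direct", with a further 10 hours indirect. The COMBiT subsection has children attending "for six hours a day, five days a week from 9am to 3pm" for two weeks.

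The claim built on this appears in two places. The Abstract (Introduction) says: "This study aims to determine the optimal density of upper limb training for children with congenital hemiplegia". The Discussion presents the trial as the first direct comparison of density, "a block of intense COMBiT compared to an equal dose of a distributed model of individualised training". The Background is more cautious and speaks only of a similar dosage.

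Study interventions also lists how the arms are meant to differ: delivery method, construct and environment. Neither total hours nor the mix of direct and indirect hours is on that list.

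**The concern.** The word indirect is used for both arms, but the declared equality counts indirect hours in one arm only. That matters because the Background's case rests on dose. It reports that mCIMT outperformed usual care given at a lower dosage, but differed little from other training given at an equivalent dose, and it infers that dose may matter more than type of therapy. If COMBiT is planned with more hours and far more direct contact, an advantage for COMBiT could be the dose effect that the Background already describes.

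What is at stake is the interpretation of a positive result. A conclusion about density at equal dose would pass from the stated aim and the Discussion into the trial report without support from the planned hours.

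**Working it through.** **Inputs, all from the protocol article**

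- COMBiT: 45 hours direct, 10 hours indirect (Abstract, Background, Study interventions, COMBiT subsection).
- COMBiT attendance: 6 hours a day, 5 days a week, 2 weeks (COMBiT subsection); 30 + 30 hours (Background).
- Standard care sessions: 6 of 1.5 hours, each made up of 1 hour of therapy and 0.5 hour on the home program (Study interventions; Standard care subsection).
- Home practice: 0.5 hour a day, 6 days a week, 12 weeks (same places).

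**Step 1: the plan's own figure**

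- Standard care direct: 6 × 1.5 = 9 hours, the same as 6 × 1 + 6 × 0.5.
- Standard care indirect: 0.5 × 6 × 12 = 36 hours.
- Standard care total: 9 + 36 = 45 hours, as stated.
- The declared equality, 45 against 45, is reproduced by setting COMBiT's direct hours alone against standard care's direct plus indirect hours.

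**Step 2: the direct and indirect categories applied to both arms**

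| Count | COMBiT | Standard care | Ratio |
|---|---|---|---|
| Direct + indirect | 45 + 10 = 55 | 9 + 36 = 45 | 55/45 = 1.22 |
| Direct only | 45 | 9 | 45/9 = 5.0 |
| Indirect only | 10 | 36 | 10/36 = 0.28 |

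Direct hours make up 45/55 = 82% of the COMBiT total and 9/45 = 20% of the standard care total. None of these three counts gives equality.

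**Step 3: does the COMBiT total close?**

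- Scheduled: 6 × 5 × 2 = 60 hours, which agrees with 30 + 30.
- Classified: 45 + 10 = 55 hours.
- Not classified: 60 − 55 = 5 hours. The article does not say what they contain. The weekly program is in an additional file that is not shown.

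**Step 4: what else differs**

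By the protocol's own list, construct (mCIMT against goal directed training), delivery (group block against individual distributed) and environment differ. Equal hours would therefore still not isolate density.

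**The case against.** The strongest reply is that indirect means different things in the two arms. In COMBiT it is general gross motor use of the arm, set apart from hours aimed at upper limb training. In standard care it is home practice of the child's goal areas, which is targeted practice without a therapist present. Under a rule of targeted upper limb practice only, the count is 45 against 45, and the bracket in Study interventions fits that reading. This has force as a guess at the intention. But the article never states the rule, and the Abstract places COMBiT's 10 indirect hours within its total dose. The rule would also leave the five-fold difference in direct hours and the differences in construct and setting untouched.

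Several stronger readings are tempting and are not supported:

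- **That the trial cannot answer its question.** The primary hypothesis and the primary aim (Methods and analyses) ask which model of training gives greater change. They mention neither equal dose nor density, and the design can test them.
- **That the COMBiT dose is really 60 hours.** Sixty is scheduled attendance. The Background wording does not require the direct and indirect parts to sum to 60. The 5 hours are a gap in classification and are not shown to be therapy.
- **That the imbalance is concealed.** The split of 45 against 9 + 36 is printed beside the claim. The fault lies in the label and the uneven count.
- **That the true ratio is about 2.** If only half of the home practice were done (an assumption), standard care would receive 9 + 18 = 27 hours, and 55/27 = 2.0. This sets incomplete adherence in one arm against full attendance in the other, and the article supports neither figure.
- **That home practice goes unrecorded.** A condensed article commonly leaves such detail to the full protocol, so its silence is no finding.

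**Conclusion.** The concern holds as a fault in the dose claim and in the interpretation built on it. By the protocol's own direct and indirect categories, planned hours are 55 against 45 in total (22% more in COMBiT) and 45 against 9 direct (five-fold), with 5 of 60 scheduled camp hours unclassified. The same-dosage and equal-dose statements are wrong as written, and the aim of determining optimal density does not follow from this comparison.

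The test of the primary hypothesis as a comparison of two models of care stands, and the sample size is not affected. What would not follow from a positive result is a claim about density at equal dose.

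The figures rest on planned hours with full delivery in both arms, and on taking the protocol's categories at face value. The 22% depends on counting COMBiT's general gross motor hours as the Abstract does. The five-fold ratio does not depend on that choice. It compares hours of direct training per child, given in a group in COMBiT and individually in standard care, so it is not a ratio of therapist time per child.

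**What to change.** 1. Define direct and indirect once. Reconcile the hours in the Abstract, the Background, Study interventions and the two intervention subsections under one counting rule applied to both arms, and classify the remaining 5 camp hours. Which hours are right is for the investigators to settle; no dose is proposed here.
2. Replace the same-dosage wording (Study interventions), the equal-dose wording (Discussion) and the optimal-density aim (Abstract) with a comparison of two models of care that differ in hours, direct contact, content, setting and schedule. Add total hours and the direct/indirect mix to the list of differences in Study interventions, and limit the conclusion accordingly.
3. Report delivered hours by arm beside the primary result, where they are recorded.

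The cost is rewording and a narrower claim. Randomisation, outcomes, sample size and the primary analysis stay as they are.

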#### ***(ii) Standard care upper limb rehabilitation***

Standard care comprises an individualised and distributed model of occupational therapy upper limb training which consists of six sessions of 1.5 hours of individual direct therapy provided in a hospital or community setting over six weeks in combination with a 12 week home program. The weekly 1.5 hour sessions comprise one hour of direct therapy, and half an hour for home program development, demonstration and training with a total dose of nine hours of direct therapy. Families will be provided with a home program to practice goal areas for 12 weeks from the commencement of individual therapy sessions (30 minutes daily practice for six days/week for 12 weeks) for a total dose 36 hours of indirect UL therapy for the standard care group. The total anticipated therapy dose for standard care including direct therapy and home program practice is 45 hours of training.

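### The arms are described as equal in dose, but under one counting rule COMBiT has 55 planned hours and standard care 45

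*Protocol article*

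**What the plan says.** **The equality claim.** The Study interventions section says "The COMBiT and the standard care programs will have the same dosages of upper limb therapy (COMBIT: 45 hours direct UL training", followed by nine direct and 36 indirect hours for standard care. It then lists three ways in which the arms differ: delivery method, therapy construct and environment. Dose is not on that list. The Discussion calls the trial the first direct comparison of training density and describes the distributed arm as an equal dose, without qualification.

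**COMBiT hours.** The article gives these four times, each time with two components:
- Abstract: "COMBiT; total dose 45 hours direct, 10 hours of indirect therapy"
- Background: "of which 45 hours was direct and 10 hours of indirect upper limb training"
- Study interventions: "Therapy will comprise 45 hours direct upper limb training and 10 hours of indirect training in more general gross motor upper limb activities"
- COMBiT subsection: "10 hours will provide indirect use of the UL in more general gross motor upper limb activities", in addition to 45 hours that directly target the upper limb

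**Standard care hours.** The total of 45 always includes both kinds:
- Abstract: "total 45 hours direct and indirect therapy"
- Background: "total dose 45 hours direct and indirect over 12 weeks"
- Standard care subsection: "The total anticipated therapy dose for standard care including direct therapy and home program practice is 45 hours of training"

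**The concern.** The statement that the doses are the same compares one arm's direct hours with the other arm's direct plus indirect hours. COMBiT's 10 indirect hours appear earlier in the same section as part of the therapy and are then left out of the comparison.

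This bears on what the trial can conclude. The Abstract gives the aim as finding the optimal density of training, and the Discussion rests the novelty of the trial on comparing density with dose held equal. The Background, reviewing earlier trials, suggests that dose rather than type of therapy may be the ingredient that matters. A reader is told that the arms differ in delivery, construct and environment but that dose is matched, and so will rule dose out as an explanation. If the planned dose is in fact larger in the arm expected to do better, that reading is wrong.

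**Working it through.** **Inputs** (all from the protocol article)

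| Quantity | Value | Section |
|---|---|---|
| COMBiT direct | 45 h | Abstract; Background; Study interventions; COMBiT subsection |
| COMBiT indirect | 10 h | same four places |
| COMBiT attendance | 6 h a day, 5 days a week, 2 weeks | COMBiT subsection |
| Standard care sessions | 6 sessions of 1.5 h | Study interventions; Standard care subsection |
| Standard care home practice | 0.5 h a day, 6 days a week, 12 weeks | Study interventions; Standard care subsection |

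**Step 1. Reproduce the stated standard care dose.**
- Direct: 6 × 1.5 = 9 h
- Indirect: 0.5 × 6 × 12 = 36 h
- Total: 9 + 36 = 45 h, as stated

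**Step 2. Reproduce the stated COMBiT figure.** The 45 hours in the equality statement are the direct hours alone. The indirect hours are not in it.

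**Step 3. Apply one rule to both arms.**

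| Rule | COMBiT | Standard care | Difference | Ratio |
|---|---|---|---|---|
| Direct plus indirect | 45 + 10 = 55 h | 9 + 36 = 45 h | 10 h | 55/45 = 1.22 |
| Direct only | 45 h | 9 h | 36 h | 45/9 = 5.0 |
| As stated (mixed) | 45 h (direct only) | 45 h (direct plus indirect) | 0 h | 1.0 |

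Only the mixed row gives equality.

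**Step 4. Check that 55 hours is plausible.** Camp attendance is 6 × 5 × 2 = 60 h, so 55 hours of therapy fit within it.

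**Step 5. Check whether anything makes up the difference.** The Concurrent therapies section rules out additional upper limb training during the study, with a return to regular therapy only after the 13-week assessments. No planned element adds 10 hours to standard care in that period.

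**The case against.** The strongest reply is that the word indirect carries two meanings. In COMBiT it describes content: general gross motor activity as opposed to targeted upper limb work. In standard care it describes delivery: goal-directed practice at home without the therapist. If the intended unit is hours of targeted upper limb practice, the comparison becomes 45 against 9 + 36 = 45, and the claim can be defended. The split is also disclosed several times, and the Background elsewhere speaks only of a similar dosage.

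Part of this stands. The contents of the two sets of indirect hours do differ, nothing is concealed, and every individual sum in the article is correct. But the content-based rule is stated nowhere, and three things tell against it:
- The Background labels the 10 hours as upper limb training, and the Abstract lists them with the total dose.
- The COMBiT subsection calls for predominant use of the impaired hand (week one) or use of both hands (week two) in all therapeutic and circus activities. On that description the 10 hours are still upper limb practice.
- The rule does not clearly give equality. Standard care's nine direct hours include 6 × 0.5 = 3 h of home programme development and demonstration. If those are not counted as practice, standard care has 6 + 36 = 42 targeted hours, not 45.

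A second reply is that density was never isolated, because the arms also differ in group v individual delivery, construct and environment. That is true, and it limits the weight of the point. But those differences are declared, whereas dose is the one factor the article says is matched. The softer wording in the Background does not correct the unqualified claims in Study interventions and the Discussion.

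**Conclusion.** The concern holds. On the article's own labels the planned doses are 55 v 45 hours (COMBiT 10 hours, or 22%, higher), or 45 v 9 hours if only direct time counts. The claim of equal dose is wrong as written, and with it the description of the trial as a comparison of density at equal dose.

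This rests on two assumptions. First, hours that the article labels indirect therapy or training count towards dose in both arms, as its standard care totals already do. Second, the figures are planned hours; hours actually delivered may differ in either arm.

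The effect is on interpretation only. The primary hypothesis, read as a comparison of two programmes, still stands, and the sample size, randomisation and analysis are untouched. It should be fixed because it changes what a positive result may be said to show.

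**What to change.** 1. In Study interventions and in the Discussion, replace the statements of same or equal dose with: *55 v 45 planned hours (45 direct + 10 indirect v 9 direct + 36 indirect)*.
2. In Study interventions, add *(iv) planned dose* to the listed differences between the arms.
3. Word the conclusion as a comparison of two programmes with unequal planned hours, not as an effect of density at equal dose.

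The cost is wording in two sections and the loss of the claim to compare density at equal dose. Neither programme needs to change, and neither do the primary hypothesis, the sample size or the analysis.
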